## **X. Sleep monitoring**

The Actiwatch Spectrum Plus (Koninklijke Philips, Amsterdam, Netherlands) has the capacity to record objective sleep activity, therefore two measures will be used to track subjective assessment of sleep during the same three time-points as the Actiwatch use (as above).

Use of a Sleep Diary is common practice in sleep research during the period of wearable sleep trackers (such as the Actiwatch) in order to corroborate objective measures of sleep. Therefore, an adapted Sleep Diary from the widely used Core Consensus Sleep Diary [39] will be used during the one week of Actiwatches to capture subjective bedtime, sleep time, nighttime awakenings, and morning rise time. 2. The Pittsburgh Sleep Quality Index (PSQI) [40] questionnaire is a retrospective self-report 10-item questionnaire that invites participants to rate their sleep quality and sleep disturbances over a one-month period. The PSQI yields a global score of sleep quality across seven domains: subjective sleep quality, sleep onset latency, sleep duration, sleep efficiency, sleep disturbances, use of sleeping medications, and daytime dysfunction, with a global score of >5 indicating poor sleep. The PSQI is considered the standard subjective sleep questionnaire and widely used and validated within the research community, found to have high internal consistency and used with both older adults and stroke patients [27, 41, 42].

The Sleep Diary and sleep questionnaire will be returned with the Actiwatch at each assessment. Completion time for both the subjective measures of sleep is expected to take between 10-30 minutes (in total), per each assessment time-point.

Changes in sleep (e.g., significantly increased or decreased total sleep time, increased sleep onset latency, decreased sleep efficiency, increased wake after sleep onset) will be used in analyses as a moderator for improvement in brain health.

## **XI. Stool sample collection for microbiome analysis**

At each timepoint, participants will be provided with a specimen kit to take home and asked to collect a stool sample. They will be asked to store the sample in the freezer until it can be returned to the facility. Participants will also receive a thermo bag to place the sample in for preservation purposes when returning it to the facility. This will be completed after each timepoint. In the case of Visit 2 (2-month timepoint), participants will complete the stool sample before they begin the exercise intervention.

The samples will be used to determine the effects of exercise on gut microbiome composition, and relationships with cognitive and brain volume change after stroke.

A portion of samples from each participant will be transferred from The Florey or Sunshine Hospital (depending on site) to Monash University for analysis by A/[name] and her laboratory team who will prepare stool samples using reagents and arrange for microbial sequencing.

It is possible that unused portions of stool samples collected in the current study will be tested for other biological markers at some stage in the future. Any further analysis of stool samples not detailed in this Protocol will be raised with Austin Health HREC if/when that time arises.

## **XII. Dietary intake monitoring**

Dietary intake will be recorded by participants using the Research Food Diary app (Xyris Software (Australia) Pty Ltd.) At the 2 month timepoint, participants who have a smart phone (Android or iOS) will receive information on the app's basic functions and how to record dietary intake on the app. Participants will complete a 3-day food diary (2-week days and 1 weekend) in the week following each timepoint: 2 months, 4 months, and 12 months. At each timepoint, participants will use the feature "share" in the app to send their 3-day food diary to the study nutritionist, who will check the food diary for completion. If any inconsistency is observed, the nutritionist will advise the Project Coordinator, who will contact the participant by phone, and corrections will be performed if necessary. Nutrient analysis will be undertaken using an Australian food composition database, the FoodWorks Professional (v8) software.

### **Qualitative sub-study – The experience of post-stroke exercise therapy**

All 120 participants in the study will be invited to participate in a qualitative descriptive sub-study that explores the experience of partaking in post-stroke home-based exercise. A semi-structured interview will be used to capture the information. Understanding the barriers and facilitators of participant engagement in post-stroke home-based exercise will assist in translating the knowledge harnessed from this project into clinical practice when prescribing post-stroke treatment and care. It will also assist in the development and formulation of future such research.

Exclusion criteria: Stroke participants with severe speech impairments or with English as their second language and which prevents effective communication (eg. severe aphasia) as determined by their treating speech pathologist will be excluded. An inability to effectively

communicate with or without an interpreter will exclude the participant from this sub-study but will not prevent participation in the overall trial.

Data collection: Qualitative data will be collected from eligible participants at the 1 year review session. Participants without stroke-related communication impairments will be asked to partake in a semi-structured in-depth face-to-face interview from a trained Associate Investigator.

Semi-structured interview guide sheets will be used to ensure all areas of interest are covered, but will allow for probing or additional questions if interesting concepts emerge. An example of the interview guide has been provided.

All interviews will be digitally audio-recorded with the participants' consent. During and/or after the interviews, field notes will be taken to add context and richness to the data collected. For example this may include notes on the time and place of the interview, whether family members are present, etc.

## 6. STUDY POPULATION

### a. RECRUITMENT PROCEDURE

120 newly acquired ischaemic stroke participants (i.e., <2 months post-ischaemic stroke) will be recruited from the Austin Health, Eastern Health, Western Health, and Epworth Camberwell Stroke Units and followed longitudinally. All ischaemic stroke subtypes will be included. Several methods will be used to recruit participants over the 3 year recruitment period of the study:

- a) The Principal Investigator ([name]) holds clinical appointments at both Austin Health and Eastern Health Stroke Units.
- b) Senior clinicians on all Stroke Units will be notified of the study and asked to identify potentially suitable participants.
- c) Study investigators will attend ward rounds and clinical meetings to identify potentially suitable participants.

In each case of the above, potential participants will be approached with the guidance of [name] or the senior inpatient ward clinician. The study investigators will speak to potential participants and provide them with verbal and written information on the study.

Participants will be screened to ensure that they are cognitively able to participate in the study and have no contraindication to the MRI. The investigators will screen potential participants using a short, semi-structured questionnaire. If the recruiter is unsure whether the potential participant has the cognitive capacity to participate, the opinions of the study neuropsychologist will be obtained.

Demographic and medical information including age, gender, medication status, side and site of stroke and admission stroke severity (National Institutes of Health Stroke Scale, NIHSS) and functional status (modified Rankin Score, mRS) will be obtained.

1001                   b. INCLUSION CRITERIA

1002 120 participants who recently acquired ischaemic strokes (i.e., ischaemic stroke <2 months)  
1003 will be recruited. All ischaemic stroke subtypes will be included.

1004  
1005 Participants will be included if the following eligibility criteria are met during the initial  
1006 screening:

- 1007 • Ischaemic clinical stroke patient (first or recurrent stroke) aged greater than 18 years;
- 1008 • Cardiac function not precluding exercise intervention;
- 1009 • Premorbid mRS<3, denoting no, mild or moderate disability; and
- 1010 • Able to give consent; and
- 1011 • Able to nominate an emergency contact person.

1012                   c. EXCLUSION CRITERIA

1013 Participants will be excluded if the following eligibility criteria are not met during the initial  
1014 screening:

- 1015 • Significant medical co-morbidities (e.g., severe cardiac disease) and/or musculo-skeletal  
1016 injuries precluding participation in exercise intervention, or making survival for 1 year  
1017 post-stroke unlikely;
- 1018 • Pregnancy;
- 1019 • Normal exclusion criteria for MRI; e.g., implanted metal, severe claustrophobia;
- 1020 • Pre-existing dementia
- 1021 • mRS >3.\*

1022  
1023 \* In order to have a cohesive cohort for this study, we have elected not to include  
1024 participants with a premorbid diagnosis of dementia or cognitive decline.

1025                   d. CONSENT

1026 Written informed consent will be obtained from participants via a Participation Information  
1027 and Consent Form (PICF). The PICF will detail the purposes of the project, issues  
1028 surrounding confidentiality and the storage and sharing of their data, potential benefits and  
1029 risks associated with their participation, and other information required for participants to  
1030 make an informed decision about their participation.

1031 A copy of the PICF will be provided to each participant to read through (i.e., in person while  
1032 they are inpatients or via mail post-discharge), and they will be given time to consider their  
1033 participation in the study within the 2-month post-stroke timeframe. As we outlined above in  
1034 Section 6 (Recruitment Procedure), participants will be screened to ensure that they have  
1035 the cognitive capacity to provide informed consent – that is, we do not intend to ask their  
1036 spouse or next-of-kin to provide informed consent on their behalf at recruitment.

1037 For those participants who do not provide signed consent during their inpatient admission, a  
1038 reply-paid envelope will be given for them to return the Consent Form once they have made  
1039 a decision. If the Consent Form is not received from potential participants within the 2 month  
1040 post-stroke time period they will be contacted via phone by one of the study investigators to  
1041 ask if they have any further questions about the study.

1042 As detailed in Section 5d (II), some participants will be invited to take part in the study after  
1043 they have been discharged. The investigator will call the participant to discuss the study and  
1044 complete the pre-study assessment questionnaire. Participants who appear eligible and are

interested in learning more about the study will be sent a copy of the PICF. They will be asked not to sign and return and consent form. The researcher will call the participant in 7-10 days to discuss the study further, and if interested, the participant may sign the consent form at this time and send it back to researchers in a reply-paid envelope, or the researcher will organise a visit to the MBC, Western Health, or The Alfred Centre to sign the consent form. Within the PICF document is a separate Consent Form for the collection of blood for the purpose of genetic analysis and biomarker analyses. Participants will have the option of Consenting to their blood being utilised for either or both of these purposes. Within the PICF is also a separate Consent Form for the collection of a stool sample for the purpose of microbiome analyses. Participants will have the option of Consenting to provide a sample for this purpose. Furthermore, participants are still able to partake in the wider study if they do not wish for blood or stool samples to be taken or be used for any of the aforementioned analyses.

In cases where a study partner is required to attend the exercise sessions, they will need to sign a separate consent form themselves.

## **7. PARTICIPANT SAFETY AND WITHDRAWAL**

### **a. RISK MANAGEMENT AND SAFETY**

There is potential for participants to experience claustrophobia and discomfort from noise in the MRI scanner; potential for discovering new/confronting information on MRI; cardiovascular events or respiratory events as a result of physical exercise; and physical injury as a result of physical exercise. Each of these risks are addressed in turn below:

#### ***Claustrophobia and discomfort from the noise of the MRI scanner***

There is potential for participants to experience claustrophobia and discomfort from the loud banging noise in the MRI scanner. These risks are outlined in the PICF.

To minimize the likelihood of an adverse reaction during the scan, participants will be asked whether they feel uncomfortable in tight spaces (e.g., elevators), or if they tend to experience discomfort in noisy environments, *before* they consent. If they indicate that they are likely to experience an adverse reaction to the scan, or if the investigator believes that this is likely to happen, it will be recommended to participants that they do not take part in the study.

Participants will be able to communicate with the radiographers at all times during the scan. If they experience any discomfort, they can notify the radiographers by pressing a buzzer, and the scan will be discontinued immediately. Participants will be able to watch movies and listen to music.

#### ***Potential for discovering new/confronting information on MRI Brain***

We are obligated to notify all participants of the results of their MRI Brain scan. The investigators will explain that there is small chance a significant abnormality, not previously known which requires further investigation, might be detected on the MRI scan. If an abnormality is detected on a scan, [name] will place a call to the participant and through their GP refer them onto appropriate members of a clinical team who are not

part of this project. [name] will also offer them counselling or other appropriate support by staff members, who, again, are not part of the project.

### ***Cardiovascular events or respiratory events as a result of physical exercise***

Although rare, two common cardiac risks include myocardial ischemia and different forms of arrhythmias. It is estimated that for adults without existing heart disease, the risk of a cardiac event or complication ranges between 1 in 400,000–800,000 hours of exercise. For patients with existing heart disease, an event can occur on average of once in 62,000 hours [43]. The exercise tests and training also involve a risk of vasovagal episodes.

To mitigate the risk of a vasovagal episode or any other significant adverse cardiac event, all participants must be cleared by a consulting physician before commencing the exercise test and exercise training intervention. The exercise testing and training will be in accordance with current guidelines from the ACSM Exercise Testing and Prescription (ACSM, 2013). [name] (Associate Investigator) is experienced in conducting exercise tests and prescribing exercise and will be responsible for training staff involved in the exercise component of the study.

This study is employing a submaximal, graded exercise test, and the exercise intervention includes CRF training at 50 to 75% of the participant's maximal aerobic capacity. It is not anticipated that the participants will be exercising at an intensity that is likely to induce significant adverse events.

Irrespective, the participant will be closely monitored at all times during the exercise test and during the exercise intervention. Participants will be required to nominate somebody the research team can contact in case of emergency during the exercise intervention. This person may also be involved as a study partner and need to attend each of the exercise intervention sessions if the Exercise Professional deems it necessary. All investigators involved in the exercise testing are required to maintain current first aid qualifications.

Participants will be educated about the procedure to follow should any concerning cardiovascular signs or respiratory signs occur off-site (i.e., not at the Austin Health campus, Eastern Health campus, Western Health campus, or The Alfred Centre ) whilst enrolled in the study. Participants will be provided with a 'Participant Adverse Event Notification Form' to document events and notify Investigators.

### ***Physical injury as a result of physical exercise***

All exercise procedures involve some risk to participants. It is possible that the participants will experience muscle soreness and stiffness as a result of completing the exercise tests and training. Such feelings are likely to subside within 24 to 48 hours after the exercise and leave no sustained muscle damage.

If participants raise concern about a physical injury sustained while participating in the study then these will be assessed by [name] (Senior Research Exercise Physiologist) or another member of the research team with appropriate training (medical doctor [e.g., [name] or [name]] or physiotherapist [e.g., [name]]).

Appropriate diagnosis and treatment will be arranged, without monetary cost to the participant, through the health service from which they were recruited.

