| 30 mins                | Balance    | Single-leg stand, Heel-to-toe walk                                                                             | 10 mins                         | Strength: Functional exercises | Sit to stand, Incline wall push-ups                                                                            |
| 20 mins                | Stretching | Active and dynamic upper and lower limb stretching                                                             | 30 mins                         | Aerobic activity               | Cycle ergometry                                                                                                |
| 5 mins                 | Cool-down  | Replication of some stretching done in warm-up                                                                 | 10 mins                         | Strength: Functional exercises | Sit to stand, Incline wall push-ups                                                                            |
|                        |            |                                                                                                                | 5 mins                          | Cool-down                      | Replication of some stretching done in warm-up                                                                 |

For participants assigned to the Balance training programme, there will be no harm to the health and well-being or detriment towards post-stroke recovery as a result of not partaking in prescribed physical fitness activities. Participants are still encouraged to undertake their usual routine leisure activities; any such activity undertaken will be captured in daily activity

diaries. Furthermore, the benefits of undertaking a Balance training programme alone is more than would have been obtained if they were not involved in this study.

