## **b. ADVERSE EVENT MANAGEMENT**

Investigators will complete an 'Adverse Event Case Report Form' to detail and monitor any cases of adverse events occurring within the study.

At each exercise session between two and four months post-stroke, and at the second and third visits (four and 12 months post-stroke, respectively), participants will be assessed for possible Adverse Events (AEs). AEs will be reported as they occur in the participant's CRF.

AEs that meet the criteria for serious, are considered Serious Adverse Events (SAEs) and will be reported for each participant for the duration of their participation in the study (i.e., between two months and 12 months post-stroke). The investigator or designee will ask the participant non-leading questions in an effort to detect adverse events, and serious adverse events.

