### ***Definition of an Adverse Event (AE)***

An Adverse Event (AE) is any untoward medical occurrence in any participant involved in the study. It does not necessarily have to have a causal relationship to the study intervention.

Examples of an AE include:

- Exacerbation of a chronic or intermittent pre-existing condition including either an increase in frequency and/or intensity of the condition.
- New conditions detected or diagnosed after involvement in the study even though it may have been present prior to the start of the study.

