### ***Time Period, Frequency, and Method of Detecting AEs and SAEs***

All AEs and SAEs will be recorded from the time of consent until the final follow up visit at one year post-stroke. Each participant will be monitored regularly by the investigator and study personnel for events occurring throughout the study.

During the study, the investigator will enquire about AEs by asking the following non-leading questions:

*"How are you feeling?"*

At subsequent scheduled intervals participants will be asked:

*"Since you were last asked, have you felt unwell or different from usual?"*

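### Falls are a foreseeable hazard of the home exercises but are neither named as a risk nor asked about, so non-injurious and out-of-session falls cannot be reliably compared by arm.

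*Protocol*

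**What the plan says.** **Risk text.** The protocol's section 7.a, under physical injury, opens generally: "All exercise procedures involve some risk to participants". The only specific harm it then names is this: "It is possible that the participants will experience muscle soreness and stiffness as a result of completing the exercise tests and training". These symptoms are expected to settle within one to two days. Assessment of an injury starts with the participant: "If participants raise concern about a physical injury sustained while participating in the study then these will be assessed by" suitably trained members of the team.

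**Exercise content.** Under section 5.b, each arm has one-hour home sessions three times a week for 8 weeks, run by an exercise professional over video. The balance session gives 30 minutes to tasks such as "Single-leg stand, Heel-to-toe walk". The fitness session has two 10-minute functional strength blocks that include sit-to-stand, plus 30 minutes of cycling. The randomisation strata in section 5.c run up to mRS 3.

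**Adverse events.** Section 7.b is broad: "An Adverse Event (AE) is any untoward medical occurrence in any participant involved in the study", whether or not it is caused by the intervention. Participants are assessed "At each exercise session between two and four months post-stroke, and at the second and third visits" (months 4 and 12). The scripted questions are "How are you feeling" and, later, "Since you were last asked, have you felt unwell or different from usual". Recording runs from consent to one year.

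**Other contacts.** Section 5.d (VII) sets telephone calls at 6, 8 and 10 months and specifies only the PASE activity questionnaire for them. Section 7.a also gives participants a form on which to notify events.

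**The concern.** Someone up to mRS 3 who stands on one leg, walks heel to toe or rises repeatedly from a chair at home about two months after a stroke may fall. The two programmes may also affect falls differently: balance tasks add exposure while they are done, and better balance could protect afterwards. The protocol gives no basis for predicting the net direction, which is a reason to count falls well in both arms.

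If a fall is recorded only when someone thinks to mention it, the count by arm mixes occurrence with reporting. The exercise professionals are unblinded (section 5.a, Blinding) and will often be the first to hear of an event. The blinded causality assessor in section 7.b sees only what was recorded. Feasibility of home exercise is a listed outcome (section 4.c), and falls bear directly on it. No analysis plan can recover events that were never elicited.

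**Working it through.** The protocol states no figure on falls, so there is nothing to reproduce. The check compares the protocol's provisions and does arithmetic on its schedule.

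**1. Are falls named?** No mention was found in the risk section (7.a), the adverse-event definition and examples or the serious-event definition (7.b), the outcomes (4.c) or the scripted questions (7.b).

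**2. Which falls do the existing routes reach?**

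| Fall | Route | Likely result |
|---|---|---|
| In session, with injury | Seen live on video; check at that session; meets the definition | Recorded |
| In session, no injury | Seen live; whether it counts as a medical occurrence is left open | Recording may vary |
| Between sessions, with injury | Next session's check, within days | Probably recorded |
| Between sessions, no injury | Question about how the person feels; participant's form | Depends on being volunteered |
| Months 4 to 12, with hospitalisation or disability | Meets the serious-event criteria | Should be recorded once known |
| Months 4 to 12, any other | Month-12 question; participant's form | Depends on recall or the form |

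A person who fell some weeks earlier without lasting symptoms can answer both scripted questions truthfully and report nothing.

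**3. Timing of adverse-event assessment** (sections 5.b and 7.b)
- Sessions: 3 per week × 8 weeks = 24.
- Visits after baseline: months 4 and 12 = 2. Total occasions: 24 + 2 = 26.
- Gap: 12 − 4 = 8 months with no scheduled assessment until the final visit.
- Share of follow-up from baseline: 8 / (12 − 2) = 80%.
- If the existing calls at months 6, 8 and 10 were used, the contacts would fall at months 4, 6, 8, 10 and 12, and the longest interval would drop from 8 months to 2.

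**4. Planned task exposure**
- Balance arm: 24 × 30 min = 720 min = 12 hours per participant. For 60 participants, 12 × 60 = 720 hours.
- Fitness arm, strength work: 24 × 20 min = 480 min = 8 hours per participant. For 60 participants, 8 × 60 = 480 hours.

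These totals assume full enrolment and attendance; the protocol itself allows for about 30% attrition over follow-up. They show that exposure is substantial and differs by arm. They do not measure missed falls.

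**The case against.** The strongest reply is that capture is good where the hazard is greatest. Sessions are watched live, participants are to be closely monitored throughout the intervention, adverse events are checked every session, and the definition covers any untoward medical occurrence regardless of cause. A home visit checks the exercise area beforehand. Participants hold a notification form. A fall that leads to hospitalisation or disability is a serious event. All of this stands for injurious falls in sessions.

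A reader might therefore go too far in several directions that the protocol does not support:
- That the questions ask only about feeling unwell. One is fully open, and the other also asks about feeling different from usual.
- That falls during the exercises themselves would generally go unrecorded. These are the best-observed falls in the study.
- That participants are often alone. The need for a study partner is decided case by case, and no frequency is given.
- That falls cannot be compared at all, or that the harms report will be too favourable. Reported falls can be counted by arm; the problem is incomplete and possibly uneven ascertainment, of unknown size and direction.

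It can also be said that non-leading questions were a deliberate choice, that falls are not an outcome, and that 7.a does not claim soreness and stiffness are the only injuries. Each is true. None of them elicits a fall without injury, or one at month 6. The general promise in 7.b of regular monitoring adds no scheduled contact. The notification form appears in the paragraph on cardiovascular and respiratory signs, and it works only if the participant sees the fall as reportable.

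**Conclusion.** The point holds for non-injurious falls and for falls outside sessions, above all between months 4 and 12. Followed as written, the question script would under-ascertain these falls, and they could not be reliably compared by arm. Injurious falls during sessions should be captured.

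The size is an ascertainment gap of 8 months out of 10, plus an undefined status for falls without injury throughout. With no fall rate in the protocol, the number of missed falls cannot be estimated.

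The conclusion assumes that the scripted questions are used as printed and that the 6-, 8- and 10-month calls cover only the PASE. The participant information form, the adverse-event CRF and the notification form were not available, so any of them may already mention falls. The change should be made, but the trial's primary analysis does not depend on it.

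**What to change.** - Name falls as a risk in section 7.a, and confirm that the participant information form does so too.
- State in section 7.b that every fall is to be recorded, whether or not it causes injury.
- Keep the open, non-leading question first. Then ask one neutral direct question, for example *Have you had a fall since we last spoke?*, at each exercise session, at the 4- and 12-month visits, and at the existing 6-, 8- and 10-month PASE calls.
- Record each fall as in session or not, and as injurious or not. Tabulate falls by arm.

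The cost is one prompted item beside an otherwise non-leading approach, one CRF field, and more minor events to record. No extra visits or staff are needed, and no rule for managing participants changes.
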